## 3. Expected Results

By conducting a retrospective observational study, we can characterize the Danish TGD youngsters over seven years. Due to our unbiased national cohort, we can provide unique and important insights into this group. Additionally, studies on gender incongruence deepen our understanding of the complexities of gender identity and expression, thereby increasing awareness and understanding of gender diversity within society and among healthcare professionals [6]. Based on our findings, we aim to optimize and tailor assessment and treatment protocols by increasing our knowledge, thus preventing harm and improving the well-being of TGD youngsters seeking healthcare.

## 4. Strengths and Limitations

This retrospective study has the considerable strength of being based on a nationwide single-center cohort, which limits selection bias from participation agreement, drop-out, regional referral, recruitment, and assessment practices. 

The data are collected systematically over a seven-year study period, allowing us to compare contemporary Danish youngsters with populations from early Dutch studies. Additionally, we can examine short-term treatment outcomes and how assessment and treatment practices have evolved during this time in Denmark.

There are no exclusion criteria for this study, as we aim to describe the entire national population of all youngsters referred to the Gender Identity Service. This approach allows us to gather a wide range of data and identify trends that might have been missed in a more restricted sample. By including all individuals in our cohort, we also reduce the risk of bias.

By describing an unselected group of youngsters with gender incongruence, we can characterize a spectrum of gender identities, including those who are not binary transgender. Additionally, we can include youngsters with gender incongruence who do not receive GAHT, which is valuable to the scientific and societal debate.

This study will provide unique initial data on our cohort, generating hypotheses and laying a foundation for future research, including potential longitudinal follow-up into adulthood.

Assessment and treatment at the Gender Identity Service were conducted as part of routine National Health Care. There will be some missing data since the data are collected retrospectively from medical records. Additionally, the list of variables and measures is limited to what can be extracted from the medical records.

The study population is limited to individuals who have attended at least one appointment at the Gender Identity Service, as there is no available data from the medical records on individuals who were referred to the Gender Identity Service but were not accepted.

## 5. Patients’ Involvement and Dissemination Strategy

The study findings will be published in peer-reviewed journals and presented at international conferences and scientific meetings. Furthermore, study findings will be presented to relevant healthcare providers, at the National Board of Health, NGOs, and patient and parent groups.

## 6. Study Registration

Clinical Trials.gov NCT06573177. Registered on 27 August 2024.

## Appendix A

**Table A1 jcm-13-06658-t0A1:** List of assessment variables to be extracted for analysis for youngsters who attended at least one appointment at the Danish Gender Identity Service from 2016 through 2022.

Assessment Variables	Value
Demographics	
Date/age at referral	Date (DD-MM-YYYY)/age in years (number)
Date/age at first appointment	Date (DD-MM-YYYY)/age in years (number)
Birth country	Denmark/other
Preterm birth	Yes/no
Adoption	Yes/no
Sex assigned at birth	Male/female
Family	
Family composition	Parents together/parents not together
Living situation	Parents/step-parents/foster parents/institution/other
Custody	Shared/mother/father/other
Siblings	Number
Twin	Yes/no
Conflicts at home	Many/few
Close relationship with parent/primary caregiver	Yes/no
Parents	
Socioeconomic status	High/mid/low
Occupation/support	Employed/student/unemployed/maternity leave/sick leave/on public welfare/on pension
Type of occupation	High-level professionals and CEOs/mid-level professionals and managers/blue-collar workers and service industry employees/unskilled laborers
Diseases	Somatic/psychiatric
School	
Type of school	Public school/special abilities school/treatment school/online school/not in school
School attendance	High/mid/low frequency
Change in school	Yes/no Number
Academic level	High/mid/low
Social skills (with classmates)	High/mid/low
Friends	
Type of friendship	Online/in real life/both
Rate of contacts	Daily/weekly/monthly/yearly
Closeness	Yes/no
Spare time	Alone/with friends/with family
Loneliness	Yes/no
Gender identity	
Gender identity	Masculine/feminine/non-binary/other
Age at onset of gender incongruence	Age in years (number) Before/during/after the onset of puberty
Social transition	Yes/partial/no
Age at social transitioning	Before/during/after the onset of puberty
Gender expression	Masculine/feminine/other
Body dysphoria	Yes/no
Family support	Yes/partial/no
Treatment wishes and expectations	Hormone therapy/operation/counseling/legal sex change/other
Fertility wishes	Biological children/adoption/no children/in doubt
Sexuality	
Sexual orientation	Male/female/non-binary/all genders/other
Romantic relationships	Yes, current/yes, prior/no
Sexual experiences	Yes/no
Number of sexual partners (lifetime)	Number
Threats and bullying	
Threats	Yes/no
Bullying	Yes/no
Violence	Yes/no
Childhood abuse	Yes/no
Sexual assault	Yes/no
Self-harm and suicidal ideation	
Self-harm	Yes, current/yes, prior/no
Suicidal thoughts	Yes, current/yes, prior/no
Suicide attempts	Yes, current/yes, prior/no
Self-reported psychiatric symptoms	
Traits of psychiatric disease	Yes, current/yes, prior/no
Psychiatric morbidity	
Prior registered diagnoses	Yes/no
Consultation at a child and adolescent psychiatric emergency room	Yes/no
Admitted to a child and adolescent psychiatric hospital	Yes/no
Pharmacological psychiatric treatment	Yes/no
Substance abuse	
Alcohol abuse	Yes, current/yes, prior/no
Smoking	Yes, current/yes, prior/no
Drug abuse	Yes, current/yes, prior/no
Self-medication	
Testosterone/estrogen/other	Yes/no
**Psychiatric Evaluation Variables**	**Value**
Psychiatric morbidity	
Registered diagnoses	Yes/no Diagnosis codes
Pregnancy and birth	Normal/abnormal
Early psychomotor development	Normal/abnormal
Psychological tests and evaluations (on indication)	K-SADS (Kiddie Schedule for Affective Disorders and Schizophrenia) [63] PSE (Present State Examination) [64] SRS-2 (Social Responsiveness Scale) [65] BRIEF (Behavior Rating Inventory of Executive Function) [66] ADHD-RS (ADHD-Rating Scale) [67] WISC 4/5 (Wechsler Intelligence Scale for Children) [68] WAIS 4 (Wechsler Adult Intelligence Scale) [69] ADOS (Autism Diagnostic Observation Schedule) [70] ADI-R (Autism Diagnostic Interview-Revised) [71] ABAS (Adaptive Behavior Assessment System) [72] SCID (Structured Clinical Interview for DSM-5 Personality Disorder) [73] Roberts [74] Rorschach [75] C-GAS (Children’s Global Assessment Scale) [76] GAPD (Global Assessment of Psychosocial Disability) [77]
**Treatment Trajectory Variables**	**Value**
Healthcare use	
Total number of visits	Number
Date of first visit	Date (DD-MM-YYYY)
Date of last visit	Date (DD-MM-YYYY)
Outcome of assessment (multidisciplinary conference decision on GAHT)	Yes/no/other
Date of discharge from Gender Identity Service	Date (DD-MM-YYYY)
**Visits Variables**	**Value**
Repeated measures	
Changes in any listed variable	

**Table A2 jcm-13-06658-t0A2:** List of treatment variables to be extracted for analysis for youngsters who attended at least one appointment at the Danish Gender Identity Service from 2016 through 2022.

Treatment Variables	Value
Basis, Department of Growth and Reproduction	
Date/age at referral for information only	Date (DD-MM-YYYY)/age in years (number)
Date/age at visit for information only	Date (DD-MM-YYYY)/age in years (number)
Date/age at referral for hormone therapy	Date (DD-MM-YYYY)/age in years (number)
Date/age at first visit for hormone therapy	Date (DD-MM-YYYY)/age in years (number)
Somatic diagnoses	Yes/no Diagnosis code
D-vitamin supplement	Yes/no Dose Date of initiation (DD-MM-YYYY) Date of cessation (DD-MM-YYYY)
Medication	Asthma medicine/allergy medicine/sleeping medicine/dermatological medicine/biological medicine/other
**Gonadotropin-releasing hormone analogs (GnRHa) Variables**	**Value**
Date/age at initiation	Date (DD-MM-YYYY)/age in years (number)
Administration route and dose	11.25 mg/12 weeks subcutaneously (SC) 11.25 mg/12 weeks intramuscularly (IM) 22.5 mg/24 weeks IM
Date/age of GnRHa cessation	Date (DD-MM-YYYY)/age in years (number)
GnRHa—repeated measures	
Date of modification of GnRHa therapy	Date (DD-MM-YYYY)
Modified dose or administration route	Dose IM
Modified interval	Weeks (number)
Side effects of GnRHa	Yes/no Headache/nausea/hot flashes/mood swings/disturbed sleep
**Gender-affirming hormone therapy (GAHT) variables**	**Value**
Date/age of initiation	Date (DD-MM-YYYY)/age in years (number)
Start of administration route	Injections IM/gel transdermal (TD)/tablets orally (PO)/patch TD
Start dose	Registered respective to the choice of drug
Discontinuation of GAHT	Discontinued by TGD-individual/discontinued by the health care team
Reasons for discontinuation of GAHT	Regret/needs more time/side effects/other
Date/age of discontinuation of all GAHT	Date (DD-MM-YYYY)/age in years (number)
GAHT, transmasculine youngsters—repeated measures	
Date of modification	Date (DD-MM-YYYY)
Modified dose or administration route	Dose IM/TD
Side effects of GAHT	Yes/no Oily skin/acne/rash/itch/breast tenderness/tenderness after injections/lower abdominal pain/other
Voice deepening	Yes/no
GAHT, transfeminine youngsters—repeated measures	
Date of modification	Date (DD-MM-YYYY)
Modified dose or administration route	Dose PO/TD
Side effects of GAHT	Yes/no Oily skin/acne/rash/itch/breast tenderness/tenderness after injections/lower abdominal pain/other
Breast development	Tanner stage B1/B2/B3/B4/B5
**Transmasculine youngsters variables**	**Value**
Puberty development a.m. Tanner	Tanner stage B1/B2/B3/B4/B5 Tanner stage PH1/PH2/PH3/PH4/PH5/PH6 Full puberty

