### 1.2. Endocrine Treatment

Puberty suppression with GnRHa can be initiated from Tanner stage 2 [58,59,60]. GnRHa is given as depot injections. GAHT encompasses estradiol in transfeminine youngsters and testosterone in transmasculine youngsters. Sex steroid treatment doses are titrated over 6 to 12 months to reach adult serum levels of estradiol or testosterone. Testosterone therapy is initiated with daily transdermal gel applications. When adult doses are reached, intramuscular depot testosterone injections are offered as an alternative. Estradiol is administered with transdermal patches, gel, or tablets, depending on personal preferences. When testosterone concentrations in transmasculine youngsters reach adult levels, GnRHa is discontinued. GnRHa is continued parallel to estradiol therapy in transfeminine youngsters until referral to adult services.

Before hormone therapy, a somatic assessment is performed, i.e., a growth chart, including bone age and growth velocity; pubertal staging, if relevant; blood pressure; routine blood samples; and whole-body Dual-energy X-ray Absorptiometry (DXA) to evaluate body composition and bone mineral density. Routine blood samples consist of reproductive and adrenal hormones, sex steroids, growth factors, vitamin D, lipids, liver and kidney parameters, hematocrit, hemoglobin, and thyroid hormones, measured by liquid chromatography-tandem mass spectrometry (LC-MS/MS) or immunoassays. Semen cryopreservation is offered to transfeminine youngsters if biologically possible. Transabdominal ultrasound (TAUS) of the internal genitalia for transmasculine youngsters is performed on indications such as breakthrough bleedings but was performed routinely after one year of testosterone therapy until 2021. Routine visits every three to six months consist of blood samples (hormones and safety parameters), growth assessment if relevant, weight, blood pressure, and exploration of treatment results, effects, and side effects. DXA scans are performed every two years; bone age is repeated if indicated. Serum, plasma, and DNA are collected for a biobank at each clinical visit.

At 18 years of age, the youngsters are referred to continued care in adult gender services at one of three centers in Denmark [57].

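### Table A2 extracts side-effect symptoms only after hormones are started, with no matching pre-treatment item, so the reported frequencies may include background symptoms

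*Protocol article*

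**What the plan says.** Appendix A of the protocol article presents Table A2 as the "List of treatment variables to be extracted for analysis". Under the heading "GnRHa—repeated measures" it records side effects of GnRHa as "Yes/no Headache/nausea/hot flashes/mood swings/disturbed sleep". Under each of the two GAHT repeated-measures headings, transmasculine and transfeminine, it records side effects of GAHT as "Yes/no Oily skin/acne/rash/itch/breast tenderness/tenderness after injections/lower abdominal pain/other".

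The source appears to be the routine visits every three to six months described in section 1.2, which include "exploration of treatment results, effects, and side effects".

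The same section describes what is done before treatment: "Before hormone therapy, a somatic assessment is performed, i.e., a growth chart, including bone age and growth velocity; pubertal staging, if relevant; blood pressure", followed by blood samples and a DXA scan. It names no symptom review. The Basis block of Table A2 holds dates, somatic diagnoses, vitamin D and a medication row ("Asthma medicine/allergy medicine/sleeping medicine/dermatological medicine/biological medicine/other").

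Section 1.3 makes the safety of hormone therapy one of the things to be described.

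**The concern.** Blood pressure, blood samples and DXA are measured before treatment, so change from baseline can be described. The listed symptoms have no such value. Several of them, such as poor sleep, mood swings, headache and acne, can occur in adolescents without any hormone. The Introduction says that depression, anxiety and ADHD are among the diagnoses most often reported in this group, and it also gives mood changes and headaches as possible adverse effects of GnRHa. The same complaint therefore has two plausible sources.

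If a symptom present before the first dose is entered in a side-effect row, the published frequency mixes background with treatment effect. Section 1 says the results should inform best practice and treatment guidelines, so a reader may take such a frequency as the harm of the drug.

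**Working it through.** The protocol article states no side-effect rate, so there is no figure to reproduce. The check is a comparison of the lists, followed by an illustration on assumed values.

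**Step 1: where the symptoms appear.**
- Table A2, GnRHa: five named symptoms, on treatment only, repeated.
- Table A2, GAHT: seven named items plus an open category, on treatment only, repeated. One of these, tenderness after injections, has no natural pre-treatment counterpart.
- Table A2, Basis block: none of these symptoms.
- Table A1: none of these symptoms. Its closing line on repeated visits covers changes in variables already on the list, so it does not reach them.
- Section 1.2, assessment before hormones: no symptom review named.

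**Step 2: what indirect baseline information exists.**
- Basis block: somatic diagnoses with codes, and sleeping and dermatological medicine.
- Table A1: one overall item on self-reported psychiatric traits (current, prior or no), registered psychiatric diagnoses, psychiatric medication, and psychological tests on indication.

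These bear on mood, sleep and skin, but none itemises headache, mood swings, disturbed sleep or acne.

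**Step 3: what comparison is possible.** Section 2.4 plans paired tests or mixed models for change over time, and reference populations for physical health. A paired comparison needs a value before treatment, which these items lack. No reference population is named for them, and the rows do not apply to untreated youngsters.

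**Step 4: possible size.** Let b be the proportion with the symptom before treatment, e the proportion of the rest in whom it newly appears, and m the share of background symptoms that are entered as side effects. Then

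recorded proportion = m × b + (1 − b) × e.

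All three are assumptions; the document gives none of them. Take e = 5% and the two limits of m.

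| b | m = 0: only new symptoms entered | m = 1: every symptom entered | Background share when m = 1 |
|---|---|---|---|
| 20% | 0.80 × 0.05 = 4.0% | 0.20 + 0.040 = 24.0% | 0.20 / 0.240 = 83% |
| 30% | 0.70 × 0.05 = 3.5% | 0.30 + 0.035 = 33.5% | 0.30 / 0.335 = 90% |
| 40% | 0.60 × 0.05 = 3.0% | 0.40 + 0.030 = 43.0% | 0.40 / 0.430 = 93% |

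With e = 0 and m = 1 the recorded proportion equals b, that is 20% to 40%. With m = 0 there is no excess. The m = 1 column is an upper case, not an estimate, and nothing in the document places m between the two limits.

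**The case against.** The strongest reply is that the variable is called a side effect, not any symptom on therapy, and that it comes from visits where treatment effects are explored. The clinician may already have left out complaints that were there before. This stands: a reader might infer that background symptoms are counted and that harms will be overstated, but the document says neither that they are counted nor that they are excluded. Incomplete notes, which section 4 expects, could also push the frequencies down, so even the net direction is not established.

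A second reply is that an attribution rule belongs in a codebook or analysis plan that is not shown. This also stands, and the absence of such a rule is not the point here. The point rests on the extraction list, which the article does publish: a later plan cannot use a baseline that was never extracted.

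Three further readings go beyond the text. The symptoms are not collected a single time, because the rows are repeated measures. Baseline information is not wholly absent, as the indirect items in Tables A1 and A2 show. Nor do the tables support the idea that GAHT would be charged with symptoms carried over from GnRHa: the two lists share no named item, so this could happen only through the open category on the GAHT list.

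Finally, section 4 says the variables are limited to what the records hold. That is a fair warning about yield, but not a reason to leave the items out. For the full programme, section 1.1 describes at least five consultations, a psychiatric screening and a paediatric endocrinology visit before the treatment decision, and Tables A1 and A2 already draw on those records.

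**Conclusion.** The point holds in a limited form. The side-effect symptoms are listed for extraction only on treatment, and no matching item is listed before it. The data as listed therefore cannot separate new from pre-existing symptoms directly, and the frequencies reported for the safety aim may include background. The size of any excess is unknown. On the assumed values above it runs from nothing to almost the whole recorded figure, depending on how clinicians wrote their notes. The conclusion assumes that the published tables are the full extraction list for these symptoms. The change is worth making because a stated aim is affected and the additions are small.

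**What to change.** 1. Extract the named GnRHa items from the last notes before the first GnRHa dose, and the named GAHT items (apart from tenderness after injections) from the last notes before the first GAHT dose. Code each as present, absent or not documented.
2. Add a field for whether a symptom on treatment is noted as worse than before.
3. Report as possible side effects only symptoms that are new or noted as worse. Report those with undocumented earlier status in a separate row, labelled as symptoms noted during therapy and not as drug effects.
4. As a check, repeat the sleep and skin items without youngsters who have sleeping or dermatological medicine recorded in the Basis block. Do this only where the entry can be dated before treatment start, because the medication row, unlike the vitamin D row, lists no start date.
5. If an illustration of the possible excess is given, present the 20% to 40% background scenario as an upper case with its assumptions stated.

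The cost is a few more fields per treated youngster, from records already being read, and one derivation rule. The main drawback is that many earlier values may be undocumented, in which case the separate row in item 3 will hold much of the data.

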Puberty suppression in transmasculine individuals leads to some regression of breast tissue growth in the early pubertal stages and cessation of menses. In transfeminine individuals, further virilization is prevented, and testicular volume may decrease. Consequently, spermatogenesis and follicle maturation are arrested [16,17,18]. Puberty suppression with GnRHa is considered reversible, allowing the resumption of pubertal development, and is well tolerated in children with precocious puberty [16,18,19,20]. This pause in physical changes prevents the progression of incongruence between body appearance and gender identity, providing a period for further clarification before starting testosterone or estradiol treatment. However, potential adverse effects include headaches, mood changes, sterile abscesses from injections, hot flushes, and fatigue [16,18,20,21,22].

Masculinizing testosterone therapy leads to cessation of menses, increase in muscle mass and strength, fat redistribution, voice deepening, growth of facial and body hair, oily skin or acne, clitoral enlargement, and increased libido. It can lead to male pattern baldness and may affect fertility [16,22,23,24,25,26,27]. Additionally, breakthrough bleeding [28] and pelvic pain [29] have been reported during testosterone therapy. Feminizing estrogen and antiandrogen treatment leads to the development of breast tissue, fat redistribution, some decrease in facial and body hair, clearer and softer skin, reduction of libido, decrease in muscle mass and strength, reduction of testicular volume and sperm quality [16,22,23,26,27,30]. While puberty suppression is reversible when stopping treatment, most effects of GAHT are irreversible, such as breast development and body hair growth. 

Research related to gender incongruence in youngsters is still sparse, and current evidence is predominantly based on studies that are more than five years old. Emerging evidence, however, suggests potential health risks associated with hormone therapy. This includes the effects of GnRHa on bone health and brain development [31], the cardiovascular risks associated with GAHT, such as dyslipidemia and venous thromboembolism, and long-term risks, such as cancer and osteopenia [16,22,27]. Furthermore, there is a knowledge gap regarding the effects of hormone therapy on youngsters, including its impact on height, the development of secondary sex characteristics, and changes in body composition [32].

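### The published GnRHa side-effect list omits two effects that the protocol itself names and has no open option, and the GnRHa modification field has no code for a change to subcutaneous injection

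*Protocol article*

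**What the plan says.** The Introduction, on puberty suppression, states that "potential adverse effects include headaches, mood changes, sterile abscesses from injections, hot flushes, and fatigue". Section 1.2 says that "GnRHa is given as depot injections", and that routine visits every three to six months cover side effects. Section 1.3 includes the safety of hormone therapy among the aims.

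Appendix A, Table A2 lists the treatment variables to be extracted, with their permitted values:

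- **GnRHa side effects (repeated):** yes/no, then "Headache/nausea/hot flashes/mood swings/disturbed sleep".
- **GAHT side effects (repeated; the same list for transmasculine and transfeminine youngsters):** yes/no, then "Oily skin/acne/rash/itch/breast tenderness/tenderness after injections/lower abdominal pain/other".
- **GnRHa route and dose at start:** "11.25 mg/12 weeks subcutaneously (SC) 11.25 mg/12 weeks intramuscularly (IM) 22.5 mg/24 weeks IM".
- **GnRHa modification:** the entry "Date of modification of GnRHa therapy", a modified interval in weeks, and a modified dose or route for which IM is the only route printed.

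**The concern.** The protocol tells the reader what harms to expect from GnRHa, then prints an extraction list that cannot name two of them and has no open category for the rest. One of the missing types is a local reaction to injection, and GnRHa is always injected.

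Clinicians are said to ask about side effects at routine visits, so the information may well be in the notes. Its type would be lost at abstraction. A table of GnRHa side effects by type would then omit sterile abscess and fatigue because the form had no place for them. A reader of the results could not tell this from their not having occurred.

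The modification field has a smaller gap of the same kind. A youngster can be recorded as starting on SC, but a later change to SC has no printed code.

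**Working it through.** There is no sample size, error rate or stated figure to reproduce. The check sets the printed lists side by side.

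**1. Effects named in the Introduction against the GnRHa field in Table A2**

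| Named in the Introduction | Code in Table A2 |
|---|---|
| Headaches | Yes (headache) |
| Mood changes | Yes (mood swings) |
| Hot flushes | Yes (hot flashes) |
| Sterile abscesses from injections | None |
| Fatigue | None |

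Coverage is 3/5 = 60%, so 2/5 = 40% of the named types have no code. This is a count of labels, not a share of harms. The table adds nausea and disturbed sleep. Disturbed sleep is not the same as fatigue, and using it as a stand-in would misclassify.

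**2. GnRHa list against the GAHT lists**

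- Open *other* option: GnRHa 0 of 1 list, GAHT 2 of 2 lists.
- Injection-related item: GnRHa 0 of 1 list, GAHT 2 of 2 lists. The item is even on the transfeminine GAHT list, although Section 1.2 describes estradiol as given by patch, gel or tablet.

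**3. Route**

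- At start: 2 routes (SC, IM). At modification: 1 route (IM).
- The corresponding GAHT modification fields each print two routes (IM/TD and PO/TD).
- Route can be worked out for youngsters who never change it and for a dated change from SC to IM. Only a later change to SC has no code.

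**4. Other fields that might recover the lost type**

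- *Somatic diagnoses* (yes/no and code) could hold a coded abscess. It sits in the basis block, with no date and no link to GnRHa, and fatigue may never receive a code.
- *Reasons for discontinuation* exists for GAHT and includes side effects. GnRHa has only a date or age of cessation.
- The GAHT injection item could catch a reaction in someone on both drugs, but would attribute it to GAHT.

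**5. What is lost, in symbols**

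Let s be the share of GnRHa recipients with any side effect, and f the share of those whose side effects are all of unlisted types. Neither is given in the article, so both are unknown between 0 and 1.

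- If abstractors tick yes without a type, the recorded overall rate is s and the loss is 0.
- If they tick no, the recorded rate is s × (1 − f), a relative loss of f.
- In either case the unlisted types have no type-specific count.

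The relative under-count of the overall rate therefore lies between 0 and f. The documents do not allow it to be narrowed.

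**The case against.** The strongest reply has four parts.

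*The Introduction is literature background and does not promise to collect every effect it mentions; Section 4 also concedes that variables are limited to what the records hold.* This is fair as far as it goes. But the limit here is set by the response list, not by the records, and safety of hormone therapy is a stated aim.

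*An article condenses, and the REDCap form may hold more.* This cannot be excluded, and it is why the point is confined to the list as published. Condensation alone is an unlikely explanation, because the same table prints *other* and an injection item for GAHT and several routes in the GAHT modification fields.

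*No comparison or model named in Section 2.4 depends on the type of GnRHa side effect.* This is correct. The damage is limited to descriptive safety reporting.

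*The consequences are easily overstated.* This also stands. A reader might infer any of the following, and the documents support none of them:

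- **Unlisted events cannot be recorded at all.** The leading yes/no item can still flag them; it is the type that is lost.
- **Sterile abscess and fatigue would be reported at 0% whatever the true rate.** A type without a category gives no estimate, and nothing in the analysis plan says that uncollected types will be reported as absent.
- **Injection reactions cannot be tied to route.** Route is known for most patterns of use. The main obstacle is that GnRHa has no injection-reaction item.
- **The number at risk of a local reaction is large.** The 12-week schedules imply 52/12 ≈ 4.3 injections a year and the 24-week schedule 52/24 ≈ 2.2. The article gives neither the number of GnRHa recipients nor any event rate, so no number at risk or number of reactions follows.

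**Conclusion.** The point holds as a gap in data capture. As published, the GnRHa list has no code for 2 of the 5 adverse effects named in the Introduction, lacks the open option that both GAHT lists have, and is paired with a modification field that cannot record a change to SC. No other listed field clearly recovers the missing information.

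Type-specific GnRHa safety reporting would be incomplete. Under-counting of the overall side-effect rate is possible but not certain: the relative loss is between 0 and f, depending on how abstractors treat unlisted types, and f is unknown.

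The conclusion assumes that Table A2 shows the response options actually available to abstractors. If it does not, the error is in the published table alone. Nothing here bears on which dose or route should be used. The change is worth making because it is cheap and serves a stated aim, but the study's main comparisons do not depend on it.

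**What to change.** 1. Add three values to the GnRHa side-effect field: injection-site reaction/sterile abscess, fatigue, and *other (text)*.
2. Let the GnRHa modification field record SC or IM, as the start field does.
3. Instruct abstractors to tick yes for any GnRHa side effect in the notes, whatever its type.
4. Re-check GnRHa visits already abstracted for these codes.
5. If the live REDCap form already has these options, correct the published list; steps 1, 2 and 4 then fall away.

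The form change is small: three values and one route option. The real cost is abstraction time for the re-check. It depends on how many GnRHa visits have been entered, which the article does not state; with visits every three to six months it may not be trivial. If time is short, the re-check could begin with visits marked yes without a type. That would not find events entered as no, and the report should say so.
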